#### 4.2 Inclusion criteria

In order to be eligible to participate in this study, a subject must meet all of the following criteria:

- Eckardt score > 3
- presence of a HRM pattern consistent with achalasia type I or II according to the latest Chicago classification (CC) criteria
- Age 7 years up to 17 years inclusive

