#### **4.4 Sample size calculation**

A recent retrospective review of 21 pediatric achalasia patients, of which 12 received POEM and 9 EBD, reported treatment success (Eckardt score  $\leq$  3) at 12, 24 and 36 months follow-up to be 100% for POEM at all follow up moments and 66.7% vs 44.4% vs 33.3% at 12, 24 and 36 months follow-up for EBD patients respectively.(16) However, in this study no repeated EBD-treatment was allowed in case of clinical recurrence. In adults 76% of patients treated according to our protocol had clinical success after 12 months.(54) Age is known to be a factor in predicting

success-rates of EBD with worse outcome in younger patients.

Taken all this together, we assumed a success rates of 72.5% for EBD and 92.5% for POEM in children after one year, we estimated that with 56 patients in each group, the study would have 80% power to detect a significant difference in success rate between EBD and POEM with a two-sided alpha level of 0.05. To cope with an estimated 10% loss to follow-up, we aim to enroll a total number of 126 patients (63 patients in each group). It is assumed that patient enrollment will be accomplished within 5 years, after approval from all local institutional review boards (IRBs).

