## **6.2 Randomization, blinding and treatment allocation**

When participants are recruited for the study, the time to consider participation is up to four weeks. Before randomization, the patient (if  $\geq 12$  years) and all legal guardians (if patients <16 years) must have signed the informed consent form.

Randomization will be performed by using a web-based program (Castor electronic data capture (EDC) system) and will be stratified per center, to reach equal number of patients treated with POEM or EBD in each center. To ensure balance of treatment groups, stratified block randomization with randomly selected block sizes in order to minimize selection bias will additionally be performed within each center. Castor EDC will generate the allocation sequence. Allocation concealment is applied to all investigators, clinicians and patients. One blinded central reader will analyze all HRM and pH-MII measurements and a second blinded central reader will analyze all barium esophagrams.

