## Baseline

At baseline, the following measurements and questionnaires will be performed:

- Standard achalasia care:
  - Body weight and height and body mass index (BMI) including respective z-scores
  - Medical history
  - PedsQL 4.0 (41, 42)
- Additional study measurements and questionnaires
  - Disease specific QoL (43)
  - Reflux disease questionnaire (44)
  - PedsQL-GI 3.0 (55)

Questionnaires regarding reflux, achalasia specific quality of life and gastro-intestinal quality of life (see Appendix A) are not currently implemented in standard achalasia care. These two questionnaires take maximum 15 minutes to fill in and are not considered burdensome for patient's psychological well-being.

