## **8 STATISTICAL ANALYSIS**

All normally distributed data will be presented as means and standard deviations (SD). Data where normal distribution cannot be assumed, will be reported as median and range.

The success rate of the two procedures and their odds ratio will be analysed using logistic regression with adjustment for stratification factors. Superiority of POEM is shown when the primary outcome (need for retreatment) is significantly lower in the POEM treatment arm (defined as  $p < 0.05$ ). Data will be shown in point estimates and 95% confidence intervals.

Comparisons between groups will be made using multiple linear regression analysis for continuous data, if necessary after (log)transformation and multiple logistic regression analysis for categorical data for secondary outcomes, adjusting for stratification factors.

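### Section 8 adjusts the continuous secondary outcomes for centre alone and leaves out the pre-treatment values the trial already collects

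*Protocol*

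**What the plan says.** Section 8 names the covariates itself. The primary outcome is "analysed using logistic regression with adjustment for stratification factors". For secondary outcomes, "Comparisons between groups will be made using multiple linear regression analysis for continuous data", after transformation if needed, and the same sentence ends with "multiple logistic regression analysis for categorical data for secondary outcomes, adjusting for stratification factors". The closing clause governs both the linear and the logistic models.

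Section 6.2 says that randomization "will be stratified per center, to reach equal number of patients treated with POEM or EBD in each center". Section 3 likewise describes a centre-stratified design. No other stratification factor is named.

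Pre-treatment values exist for most continuous secondary outcomes. Section 6.3 opens its Baseline part with "At baseline, the following measurements and questionnaires will be performed" and lists PedsQL 4.0, the disease-specific quality-of-life questionnaire, RDQ and PedsQL-GI. Eckardt and HRM come from the diagnostic work-up: section 4.2 requires "Eckardt score > 3" and "presence of a HRM pattern consistent with achalasia type I or II", and Figure 1 in the Summary lists both before therapy.

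After treatment, Figure 1 and section 2 place the questionnaires and Eckardt score at 3, 6 and 12 months. Scheduled HRM and pH-MII are at 12 months only (section 6.3, Follow-up).

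**The concern.** A comparison of follow-up scores that ignores the same score before treatment leaves between-child variation in the residual that the baseline value could explain. Randomization keeps the comparison unbiased, but the interval is wider than necessary, and the estimate is not corrected for a chance difference between the arms at baseline.

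This matters most for quality of life and reflux symptoms. The Summary concludes from adult and limited pediatric data that POEM seems more effective at the price of more reflux disease, and leaves open which treatment gives children the better quality of life. Those scores are secondary outcomes, and the sample size was set for retreatment rather than for them. Section 4.4 foresees five years of enrolment, so precision cannot easily be bought with more patients.

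**Working it through.** **Inputs from section 4.4.** Success 72.5% (EBD) and 92.5% (POEM), two-sided alpha 0.05, power 80%, 56 evaluable per arm, 10% loss, 126 enrolled.

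**The plan's own figure.** Two proportions, pooled variance, no continuity correction. The mean proportion is 0.825.
- n = [1.960 × √(2 × 0.825 × 0.175) + 0.842 × √(0.725 × 0.275 + 0.925 × 0.075)]² / 0.20² = (1.053 + 0.436)² / 0.04 ≈ 55.5, so 56 per arm.
- 56 / 0.90 = 62.2, so 63 per arm and 126 in total.

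The figure reproduces. It does not depend on covariates, so this point leaves the sample size untouched.

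**Detectable difference in a continuous outcome, without the baseline value.** With 56 per arm and 80% power: (1.960 + 0.842) × √(2/56) = 0.53 SD.

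**With the baseline value.** If r is the correlation between pre-treatment and follow-up values, residual variance is multiplied by 1 − r² and the detectable difference by √(1 − r²). An effect that has 80% power unadjusted then has power Φ(2.802/√(1 − r²) − 1.960). The equivalent number per arm is 56/(1 − r²). The protocol gives no r, so the range is assumed.

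| r (assumed) | Variance factor | Fall in variance | Detectable difference (SD) | Power | Equivalent n per arm |
|---|---|---|---|---|---|
| 0.2 | 0.96 | 4% | 0.52 | 81.6% | 58.3 |
| 0.3 | 0.91 | 9% | 0.51 | 83.6% | 61.5 |
| 0.5 | 0.75 | 25% | 0.46 | 89.9% | 74.7 |
| 0.7 | 0.51 | 49% | 0.38 | 97.5% | 109.8 |

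**Price of the extra term.** It uses one residual degree of freedom. With 112 evaluable patients and two arm means there are 112 − 2 = 110 before centre terms, so a baseline value with no correlation at all costs about 1/110 ≈ 0.9% of variance. The number of centres is not stated; centre terms would raise this slightly.

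**Age in the primary logistic model, checked separately.** Expected retreatment events are 56 × (0.275 + 0.075) = 19.6. A simulation used 2,000 trials per scenario, 56 per arm and a likelihood-ratio test. It added one standardised covariate with an assumed odds ratio per SD and left out centre terms.

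| Covariate acts in | OR per SD | Power without | Power with |
|---|---|---|---|
| neither arm (two runs) | 1.0 | 84.1%; 83.2% | 83.2%; 82.3% |
| EBD arm only | 1.5 | 83.6% | 83.2% |
| EBD arm only | 2.0 | 83.7% | 83.7% |
| EBD arm only | 3.0 | 83.4% | 84.3% |
| both arms | 1.5 | 85.2% | 85.4% |
| both arms | 2.0 | 84.8% | 85.7% |
| both arms | 3.0 | 84.5% | 87.8% |

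The change runs from about −1 to +3 points. The median standard error of the log odds ratio rises in every scenario, from about 0.60 to between 0.60 and 0.67. Any gain in power comes from the estimate moving away from zero, not from a narrower interval.

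**The case against.** The strongest reply is that nothing here is wrong. Adjusting for the stratification factor matches the design and gives a valid test. Covariates for secondary models are often left to an SAP, and section 8 does not forbid further terms. All of that is true, and it makes this an improvement rather than the correction of an error. What it does not remove is that section 8 chooses a covariate set. An SAP that followed it would compare follow-up scores without their baselines.

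The size is also open to challenge. No correlation is documented, and r = 0.7 is doubtful for Eckardt: entry truncates the score above 3, while the assumed success rates put most follow-up scores at 3 or below. HRM is restricted to types I and II, which may also lower r. The questionnaire scores are not selected on in this way.

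A reader might go further and infer that leaving age out of the primary model widens its interval, since section 4.4 says "Age is known to be a factor in predicting" EBD success. The documents do not support that. Adding a covariate to a logistic model does not narrow the interval for the log odds ratio. The age figures given are adult ones, with a cut-off at 40 years (Summary and section 1), and no effect is given within ages 7 to 17. With about 20 expected events and centre terms already in the model, extra terms also have a cost there. Setting later balloon sizes by age below or above 12 (section 5.1) does not show that age predicts outcome.

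**Conclusion.** The point holds for the continuous secondary outcomes that have a pre-treatment value: PedsQL, PedsQL-GI, the disease-specific score, RDQ, Eckardt and the HRM parameters. Omitting that value forgoes a variance reduction of r², which is 4% to 49% over the assumed range of 0.2 to 0.7. The lower end is more plausible for Eckardt. The larger gains should not be quoted as expected, because they rest entirely on the assumed correlation.

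The point does not reach the sample size or the validity of the planned tests. It also does not extend to pH-MII, which has no planned baseline. A reader might assume that HRM too could be modelled over 3, 6 and 12 months, but scheduled post-treatment HRM is at 12 months only.

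Age in the primary model is a matter of choice: about −1 to +3 points of power under assumed effects, and no narrower interval.

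**What to change.** Amend section 8 along these lines:

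*Each continuous secondary outcome with a pre-treatment measurement is analysed with that value as a covariate, alongside centre. For PedsQL, PedsQL-GI, the disease-specific score, RDQ and Eckardt this is ANCOVA at each time point, or a repeated-measures model over 3, 6 and 12 months with baseline, visit, treatment, treatment by visit, and centre. For HRM parameters it is ANCOVA at 12 months. pH-MII parameters are adjusted for centre only.*

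If an outcome is log-transformed, its baseline value should enter on the same scale, and a rule for a missing baseline value should be stated so that patients are not lost from the model. If age is wanted in the primary model, it should be prespecified as a single continuous term, without a claim of greater precision.

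The cost is wording in the protocol or SAP. No new visit, test or questionnaire is needed.

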## **9 ETHICAL CONSIDERATIONS**

### **9.1 Regulation statement**

The study will be conducted according to the principles of the Declaration of Helsinki (WORLD MEDICAL ASSOCIATION DECLARATION OF HELSINKI Ethical Principles for Medical Research Involving Human Subjects, 2008).

### **9.2 Recruitment and consent**

Patients who visit the Pediatric Gastroenterology departments of the participating centers will be approached. Eligible patients and their parents will be given an explanation of the study. Each patient and his/her legal guardians will receive an information brochure about the study and an informed consent form for participation. They will be given the time needed to read the information and ask questions. Study procedures or randomization are only initiated *after* the informed consent form has been signed. When participants are recruited for the study the time to consider participation in the study is 1 – 4 weeks.

Written informed consent form (ICF) is signed by all legal guardians (parents/caregivers), and/or patient, depending on patient's age:

- Children < 12 years: ICF signed by all legal guardians.
- Children 12 – 16 years: ICF signed by all legal guardians and patient
- Children ≥ 16 years: ICF signed by patient

In daily practice, the study subject is often joined by only one parent at the outpatient clinic. Therefore, the other parent is allowed to sign the ICF form at home before- or after the hospital visit. As long as both signatures are collected, this is acceptable. In situations where only one parent/legal guardian is known or if one parent is deceased, the absence of the second signature is explained on a Note-to-File or in the patient's electronic patient file. A copy of the signed informed consent form is given to the participant.

### **9.3 Objection by minors or incapacitated subjects (if applicable)**

Objection of minors will be evaluated according to the 'Code of conduct relating to expressions of objection by minors participating in medical research'. Approved by the Board of the Netherlands Association for Pediatric Medicine and published in the newsletter no. 3, June 2001. (57)

### **9.4 Benefits and risks assessment, group relatedness**

If a pediatric patient is diagnosed with achalasia, invasive treatment is always needed (i.e. LHM, POEM or EBD). Because EBD and POEM are currently both used as therapeutic options for children with achalasia, children will not have any additional risk when participating in this trial. Although subjects will be managed similarly to patients who are not enrolled in this study, participating this study may be beneficial because of our strict follow-up scheme. Potential treatment failure can therefore be detected in an early stage and additional therapy can be offered early after symptom recurrence. On the other hand, our follow-up scheme can be burdensome as it involves additional time needed to fill in questionnaires that are additional to current standard clinical care.

As only small and often retrospective studies are available about pediatric achalasia therapy, it is unknown how children should best be treated. It is therefore important to compare the two least invasive therapies (i.e. EBD and POEM) in children, to improve future therapeutic strategies in pediatric achalasia.

#### **Risk and complications of EBD**

EBD is a frequently performed procedure in children with achalasia but on the long-term, re-dilations are often needed (see introduction and rationale).(19-21, 26) Complications due to EBD are uncommon and include perforation (data from retrospective pediatric studies: n=5/209 and 1/60 respectively(26)), post-procedural pain (n=1/10) and fever (n=2/10). Therapy for

perforations is mostly conservative with food and drink restriction and intravenous antibiotic therapy.

#### Risk and complications of POEM

POEM is a relatively new procedure in the treatment of achalasia. Results from both pediatric and adult studies indicate that POEM seems to be a promising new treatment for pediatric patients with achalasia, resulting in long-term symptom relief, without serious adverse events and with potential beneficial influence on QoL.

POEM has been shown a feasible and safe procedure in children.(10, 11, 16, 36-38) The largest pediatric study included 27 individuals with success achieved in 26 during two years of follow-up in the absence of serious adverse events or special technical difficulties.(10)

Serious adverse events that could theoretically occur during the procedure are bleeding or esophageal perforation. Treatment of these complications can instantaneously be performed during the procedure by clipping the bleeding vessel or perforation. In exceptional cases a surgical procedure could be needed. The largest cohort study in children (n=44, follow-up 1 – 53 months) reported only mild intraoperative complications including retroperitoneal CO2 (7%), capnoperitoneum (3%), and mucosal injury (1%). Pneumoperitoneum can be relieved by a puncture during the procedure. Postoperative retroperitoneal CO2 is usually self-limiting and additional treatment is not needed. So far the only complications that occurred in the treated (adult and pediatric) patients of the Amsterdam UMC, location Academic Medical Center (AMC) consisted of minor bleedings that were stopped during the procedure and one patient developed a pneumoperitoneum which was relieved during the procedure.

All the additional measurements that are performed before and after treatment are safe procedures and routinely performed in the clinical setting. Possible complications are mainly due to placement of the catheters and endoscope. The catheters can give minor discomfort in the nose and pharynx. Furthermore in rare cases a mucosal bleeding of the nose, caused by the catheter, can occur which never needs additional treatment. The endoscope can cause some discomfort in the

pharynx after the procedure.

#### Risks due to COVID-19 pandemic

Participants of this study will not be exposed to additional Covid-19 risks compared to peers with achalasia who do not participate in this study, as the studied procedures (EBD and POEM) are part of standard medical care. If necessary, outpatient clinic visits at T=3, 6 and 12 months can be rescheduled as a “video consult”. If, due to COVID-19, additional testing for study procedures at T=12 months are not possible to perform, we will note this in our database as a protocol deviation. If a participant experiences recurrent symptoms and additional testing is needed as part of standard clinical care, these measurements will be scheduled and additional precautionary measures for Covid-19 will be taken.

### **9.5 Compensation for injury**

The sponsor/investigator has a liability insurance which is in accordance with article 7, subsection 6 of the WMO.

The sponsor (also) has an insurance which is in accordance with the legal requirements in the Netherlands (Article 7 WMO and the Measure regarding Compulsory Insurance for Clinical Research in Humans of 23th June 2003). This insurance provides cover for damage to research subjects through injury or death caused by the study.

The insurance applies to the damage that becomes apparent during the study or within 4 years after the end of the study.

### **9.6 Incentives**

Patients participating in this study will not receive any form of financial compensation

## **10 ADMINISTRATIVE ASPECTS, MONITORING AND PUBLICATION**

### **10.1 Handling and storage of data and documents**

The data of the subjects are coded in order of participation. The code can only be seen by the investigators. The code and the data are stored in different locations. Data is captured in an online medical research database (Castor) that is ISO 27001 and ISO 9001 certified.

Qualified authorities can get insight in code and data, but only when accompanied by the investigators. Data will be stored 20 years after closure of the trial, in order to enable long-term follow-up of this cohort until all patients have reached adulthood. All personal data is protected conform the reules of the General Data Protection Regulation.

### **10.2 Handling and storage of data and documents**

Monitoring in the Amsterdam UMC will be performed by the Clinical Research Unit of the Amsterdam UMC-AMC.. Monitoring of other sites will occur locally according to local legislation and agreements with the local ethical committee.

Data monitoring will be performed by a certified clinical research associate of the participating institute or its delegate. The monitor will compare the data entered into the database with the hospital or clinic records (source documents). The nature and location of all source documents will be identified to ensure that all sources of original data required to complete the database are known to the investigational staff and are accessible for verification. Frequency of monitoring will be further discussed with the monitoring party.

### **10.3 Amendments**

Amendments are changes made to the research after a favorable opinion by the accredited MREC has been given. All amendments will be notified to the MREC that gave a favorable opinion.

### **10.4 Annual progress report**

The sponsor/investigator will submit a summary of the progress of the trial to the accredited MREC once a year. Information will be provided on the date of inclusion of the first subject,

numbers of subjects included and numbers of subjects that have completed the trial, serious adverse events/ serious adverse reactions, other problems, and amendments.

#### **10.5 Temporary halt and (prematurely) end of study report**

The investigator/sponsor will notify the accredited MREC of the end of the study within a period of 8 weeks. The end of the study is defined as the patient's last visit.

The sponsor will notify the MREC immediately of a temporary halt of the study, including the reason of such an action.

In case the study is ended prematurely, the sponsor will notify the accredited MREC within 15 days, including the reasons for the premature termination.

Within one year after the end of the study, the investigator/sponsor will submit a final study report with the results of the study, including any publications/abstracts of the study, to the accredited MREC.

#### **10.6 Public disclosure and publication policy**

The General Assessment and Registration Form (ABR-form) will be filled in to provide transparency with regard to this trial. This study is also registered in the ISRCTN ([www.isrctn.com](http://www.isrctn.com)). The study results will be made public by submission/publication in international journals and at scientific meetings.

